### Trial design

This study is designed as a three‑arm, parallel‑group RCT with a 1:1:1 allocation ratio. Hospitals (Shohada‑ye Tajrish, Taleghani, and Imam Hossein) are the desired study settings. The trial will be conducted within a superiority framework to compare the effectiveness of the educational interventions across the study arms.

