### Sample size

Due to the absence of previous studies closely matching the design and interventions of the present trial, the sample size calculation will be based on data obtained from a preliminary pilot study that the research team will conduct. A pilot study will be conducted in the same dialysis units as the definitive three-arm trial. It aims to (1) estimate parameters required for sample-size calculation (primary-outcome SD), (2) assess recruitment and retention rates, (3) measure patient adherence and provider fidelity, (4) evaluate methodological contamination, and (5) identify operational or data-quality problems.

The selection of this approach ensures that the sample size possesses sufficient statistical power to identify clinically relevant differences between groups, taking into account the unique features of both the study population and the interventions.

Participants will be screened consecutively using the same inclusion/exclusion criteria as in the primary protocol, provide informed consent, and be randomized to one of three arms. The intervention principles, outcome instruments, and timepoints will be identical to those in the definitive trial. For feasibility-only objectives, approximately 12 participants per arm (36 total) will be recruited [38]; if variance estimation is required, around 35 per arm (105 total) will be targeted [38].

A pilot report will document parameter estimates and operational findings. Pilot outcomes include: Standard Deviation (SD) and 95% Confidence Interval (CI) of the primary outcome, recruitment and retention proportions, adherence categories, fidelity scores from structured checklists, contamination based on self-report and digital access logs, and data-quality indicators (missing data, questionnaire burden, technical issues).

Pilot estimates will inform the definitive sample size, attrition-adjusted recruitment targets, and possible design modifications if contamination is substantial. Any changes to the main trial will be justified, approved, and reported. The sample size will be estimated using the pilot data, with a significance level of 0.05 (two-sided) and a statistical power of 80%. The total estimates will be allocated equally across the three study groups. By relying on pilot data without prior literature, the study design ensures methodological rigor and optimizes resource use while maintaining sufficient power to address the primary research objectives.

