### Interactive video education arm

The educational intervention will be delivered in two sequential phases over a total duration of six hours. A cohort of participants will be enrolled and organized into groups of five, each group facilitated by a certified instructor with expertise in interactive video pedagogy.

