### Conventional video education arm

The educational intervention will be delivered in two sequential phases over a total duration of six hours. Participants will be enrolled and organized into cohorts of five participants, each facilitated by an experienced instructor conversant with video-based teaching methods.

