### Separate workshops and facilitators

Consolidation workshops shall be scheduled separately for each study arm, with dedicated facilitators appointed to each group. Facilitators will be instructed to refrain from sharing educational materials across groups.

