### Statistical analysis

The baseline characteristics will be summarized using descriptive statistics (mean ± SD, frequency, and percentage). Primary and secondary outcomes will be analyzed using longitudinal data analysis methodologies, accommodating repeated measures collected at four time points (baseline, immediate post-intervention, one-month, and three-month follow-up) and across three intervention groups. Depending on the attributes and distribution of the dependent variables, consideration will be given to both mixed models for repeated measures (MMRM) and generalized estimating equations (GEE).

MMRM will be applied to model continuous normally distributed outcomes, incorporating fixed effects for group, time, and their interaction, with an appropriate covariance structure to account for within-subject correlations. GEE will be used as an alternative approach, particularly for outcomes with non-normal distributions or when robust population-averaged effects are of interest. MMRM and GEE will be chosen based on model fit and assumptions.

Analyses will be conducted under the intention-to-treat principle. Missing data will be addressed using multiple imputations, assuming they are randomly missing. Effect measures, CI, and a significance level of p < 0.05 will be reported. Adjusted analyses may include relevant covariates, with the primary analysis specified accordingly.

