The present trial directly addresses these evidence gaps by comparing interactive video, conventional video, and routine education. We hypothesize that the inherently active nature of interactive videos—with personalized feedback, problem‑solving scenarios, and opportunities for active response—will more effectively enhance patient activation and yield greater improvements in patient activation and treatment adherence (particularly in the challenging domains of dietary and fluid management) and, consequently, interdialytic weight control. Prior studies have demonstrated that videos incorporating advanced interactive features (e.g., domain‑specific questions and tasks) are significantly more effective than those offering only basic navigation interactivity or none at all [49]. A recent meta‑analysis reported an overall effect size of Hedges’s g = 0.522 in favor of interactive video interventions, consistent with active learning theories that posit superior outcomes for learner‑engaged modalities [49]. Furthermore, interactive video learning—leveraging multimedia, engagement, and customized content—has been recognized as an effective instructional tool that enhances knowledge acquisition, motivation, and user engagement. This approach, therefore, offers a scalable, cost‑effective strategy for patient education in clinical settings.

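### Both video arms meet in instructor-led workshop groups of five, but the stated model and sizing rule allow for no correlation within those groups

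*Protocol article*

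**What the plan says.** The trial randomises individual patients to three arms "with a 1:1:1 allocation ratio" (Trial design). After randomisation, interactive-video patients are "organized into groups of five, each group facilitated by a certified instructor", and conventional-video patients are "organized into cohorts of five participants, each facilitated by an experienced instructor". In each video arm, ten 30-minute modules are taken through a platform (five hours), and the assigned group then meets for a one-hour workshop led by the instructor. The usual-care section describes nurse instruction, pamphlets and nurse follow-up, with no groups of this kind.

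The Statistical analysis section gives a mixed model for repeated measures over four time points, baseline included. It has fixed effects for arm, visit and their interaction, "with an appropriate covariance structure to account for within-subject correlations". GEE is the alternative. No term for workshop group or facilitator is named.

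The Sample size section will set N from a pilot, "with a significance level of 0.05 (two-sided) and a statistical power of 80"%. The pilot's first aim is to "estimate parameters required for sample-size calculation (primary-outcome SD"). Its listed outputs contain no measure of correlation within groups.

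The section on separate workshops schedules them by study arm, "with dedicated facilitators appointed to each group". The section on instructor bias relies on a script, training, a competency test and fidelity checks, so that differences can be put down to the interactive video and not to the facilitator.

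**The concern.** Grouping that arises after individual randomisation still induces correlation. Patients in one workshop share an instructor, a discussion and each other's contributions, so their later activation scores may be more alike than those of patients in different groups. A model that allows only for repeated measures within a patient treats the patients in a workshop as independent. With any positive within-group correlation, and other things equal, its standard errors are too small. GEE does not cure this if its cluster is the patient.

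The contrast most exposed is interactive versus conventional video, because both arms are grouped. It is also the comparison that the Introduction and Discussion present as the reason for the trial. Sizing on the SD alone has the matching fault: the sample would be too small to give 80% power once the test is made valid.

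A second consequence follows if facilitators work in one video arm only. Differences between facilitators then form part of the arm contrast, and no model can separate them from the effect of the video format.

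**Working it through.** **Inputs from the protocol.** Two-sided alpha 0.05; target power 80%; equal allocation; group size 5 in each video arm; no groups described in usual care.

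**Inputs the protocol does not give.** N, SD, target difference and ICC. There is therefore no planned N to reproduce. The ICC is an assumption, shown at 0.01, 0.05 and 0.10.

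**Step 1: why N is not needed.** Any two-arm comparison with exactly 80% power at two-sided 0.05 has a true difference of 1.960 + 0.842 = 2.802 standard errors, when the standard error assumes independence.

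**Step 2: variance factor F.**
- Video versus video, both arms grouped: F = 1 + (5 − 1) × ICC, which gives 1.04, 1.20 and 1.40.
- Video versus usual care, one arm grouped: F = (1 + [1 + 4 × ICC]) / 2 = 1 + 2 × ICC, which gives 1.02, 1.10 and 1.20.

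The unadjusted standard error is 1/√F of its true value. For video versus video that is 98%, 91% and 85%.

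**Step 3: two different tests, kept apart.**
- Planned, unadjusted test: type I error = 2 × [1 − Φ(1.960/√F)]; power = Φ(0.842/√F).
- Correctly adjusted test on the same N: type I error 5%; power = Φ(2.802/√F − 1.960).

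| Contrast | ICC (assumed) | F | Unadjusted: type I error | Unadjusted: power | Adjusted: power |
|---|---|---|---|---|---|
| Interactive vs conventional | 0.01 | 1.04 | 5.5% | 79.5% | 78.4% |
| | 0.05 | 1.20 | 7.4% | 77.9% | 72.5% |
| | 0.10 | 1.40 | 9.8% | 76.2% | 65.8% |
| Video vs usual care | 0.01 | 1.02 | 5.2% | 79.8% | 79.2% |
| | 0.05 | 1.10 | 6.2% | 78.9% | 76.2% |
| | 0.10 | 1.20 | 7.4% | 77.9% | 72.5% |

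Worked line for ICC 0.05, video versus video: 1.960/√1.20 = 1.789, two-sided tail 7.4%; 0.842/√1.20 = 0.769, Φ = 77.9%; 2.802/√1.20 − 1.960 = 0.598, Φ = 72.5%.

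**Step 4: simulation check.** With 60 patients per arm in 12 groups of 5 and 20,000 runs, the unadjusted t-test of video versus video rejected a true null in 7.3% of runs at ICC 0.05 and 9.7% at ICC 0.10. For video versus usual care the figures were 6.3% and 7.4%. These agree with the formulas.

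**Step 5: effect on N, for illustration only.** The protocol's one effect size is a cited meta-analysis value in the Discussion ("g = 0.522 in favor of interactive video interventions"), which is not adopted as the trial's target. It would need 58 per arm under independence. Multiplying by F for the video-versus-video contrast gives 58 × 1.04, × 1.20 and × 1.40, that is 61, 70 and 82 per arm.

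**Step 6: larger clusters.** The number of groups per facilitator is not given. If one facilitator taught 20 patients (assumed) and the ICC at facilitator level were 0.02, then F = 1 + 19 × 0.02 = 1.38, with type I error 9.5% unadjusted and power 66.5% adjusted.

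**The case against.** The best case on the other side is that the correlation may be very small. Five of the six hours are modules taken on a platform. The conventional-arm instructor does not interrupt playback, and the workshop follows an exact script with a competency threshold of 85% and a check against added content. This stands, and it makes a low ICC plausible. At 0.01 the loss is trivial. It does not make the model right at higher values, and the protocol does not claim that the correlation is zero.

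A reader might infer that the standard errors are certainly too small and that the 80% power is certainly missed. The documents do not support that. They give no N, SD, difference or ICC, and 80% is a target for a calculation still to come. A reader might also infer that the planned test suffers both the inflated type I error and the fall in power to 65.8%. It does not: that power belongs to the adjusted test, and the planned test's own power falls only to about 76.2% at ICC 0.10.

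Three further points stand in part. Usual care relies on unit nurses and a dedicated follow-up nurse, so some provider clustering is possible there. The usual-care figures above assume none. Randomisation is stratified by hospital and dialysis shift, and these factors are not named in the model; leaving them out tends to enlarge standard errors and could offset part of the effect. A separate analysis plan might add a group term, but the article itself states which correlation its model handles and which parameter sizes the trial, and neither allows for the groups it creates.

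The section on instructor bias states the aim of the fidelity procedures, not a result. The point there is only that the aim cannot be fully met by design if facilitators are specific to an arm.

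**Conclusion.** The point holds in conditional form. The omission is plain in the text: groups of five in both video arms, a model that accounts only for within-subject correlation, and a sizing rule that names only the SD. The direction holds for any positive within-group correlation, other things equal. The size cannot be established from the protocol. For interactive versus conventional video it runs from negligible at ICC 0.01 to nearly double the nominal type I error at 0.10, and it is about half as large for a video arm versus usual care.

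The figures assume full groups of five, one level of clustering, no clustering in usual care, and a contrast that behaves like a difference between two means. Clusters are larger, and the effect grows, if one facilitator leads several groups. The matter needs settling before enrolment, because workshop membership that was never recorded may not be recoverable at the analysis stage.

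**What to change.** - **Data:** record workshop group and facilitator for every participant in the video arms.
- **Primary model:** add a random effect for workshop group in the two video arms only (a partially nested model), with Kenward-Roger or Satterthwaite degrees of freedom. Let it act on post-baseline outcomes only. Baseline is one of the repeated outcomes and is measured before any group has met, so a plain random intercept would impose a correlation that cannot yet exist.
- **Sensitivity analysis:** repeat the analysis with clustering by facilitator.
- **Sample size:** when sizing from the pilot, apply 1 + (5 − 1) × ICC to the video arms over a range of ICCs, or restate the power. Do not rely on a pilot estimate of the ICC: 12 to 35 patients per arm is only about 2 to 7 groups.
- **Wording:** unless facilitators serve both video arms, qualify the section on instructor bias to say that the interactive versus conventional contrast may include facilitator differences.

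The cost is two data fields, one random effect, and slightly wider intervals, with either a larger sample or a lower stated power.

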## Discussion

The present protocol outlines an RCT with three parallel groups to evaluate and compare the effectiveness of interactive versus conventional video-based education on patient activation, treatment adherence, and IDWG in HD patients. This study addresses significant gaps in existing knowledge and provides high-quality evidence to support educational interventions in this vulnerable population.

Patients undergoing HD encounter multifaceted difficulties in managing stage 5 CKD, necessitating rigorous compliance with stringent treatment protocols, encompassing pharmaceutical consumption, fluid and dietary limitations, and consistent dialysis appointments. Lack of compliance with these therapies could precipitate serious health issues, frequent inpatient care, and a marked decrease in one’s well-being. Interventions of an educational nature play a pivotal role in fostering patient self-management and enhancing clinical outcomes [47].

Available systematic reviews have revealed that digital health interventions (DHIs) are associated with “small to large” gains in treatment adherence among dialysis patients. Nonetheless, the quality of extant evidence is often assessed as “low to moderate,” and the quantity of included trials is limited, thereby emphasizing the necessity for more comprehensive investigation. In particular, gains in dietary adherence and fluid management have been described as only “moderate” and “small,” respectively [48], suggesting that these domains may benefit from more specialized interventions and direct support. Moreover, a traditional educational study in CKD patients undergoing HD—despite reporting significant improvements in knowledge and adherence to fluid, dialysis, and medication regimens—found no statistically significant change in dietary adherence or pre-dialysis weight [47]. This indicates that knowledge enhancement alone is insufficient to alter complex behaviors such as dietary and fluid management, highlighting the need for more innovative approaches.

The present trial directly addresses these evidence gaps by comparing interactive video, conventional video, and routine education. We hypothesize that the inherently active nature of interactive videos—with personalized feedback, problem‑solving scenarios, and opportunities for active response—will more effectively enhance patient activation and yield greater improvements in patient activation and treatment adherence (particularly in the challenging domains of dietary and fluid management) and, consequently, interdialytic weight control. Prior studies have demonstrated that videos incorporating advanced interactive features (e.g., domain‑specific questions and tasks) are significantly more effective than those offering only basic navigation interactivity or none at all [49]. A recent meta‑analysis reported an overall effect size of Hedges’s g = 0.522 in favor of interactive video interventions, consistent with active learning theories that posit superior outcomes for learner‑engaged modalities [49]. Furthermore, interactive video learning—leveraging multimedia, engagement, and customized content—has been recognized as an effective instructional tool that enhances knowledge acquisition, motivation, and user engagement. This approach, therefore, offers a scalable, cost‑effective strategy for patient education in clinical settings.

### Strengths and limitations

By employing a three‑arm parallel RCT design, this study provides the highest level of evidence for determining the relative effectiveness of the educational interventions. Balancing observed and unobserved participant characteristics achieved through randomization minimizes bias and enables a precise evaluation of causal relationships between interventions and outcomes. This design allows for causal inference and minimizes bias [50]. Moreover, high‑quality protocols promote proper trial conduct, minimize avoidable protocol amendments, and facilitate comprehensive evaluation of scientific and ethical considerations. Having a standard video group and routine care control enables precise assessment of the added value of interactive video beyond mere information delivery or usual care. This comparative analysis distinguishes authentic intervention outcomes from confounding variables, thus affording a more comprehensive understanding of the relative effectiveness of various educational methodologies. A rigorous literature review and content validation ensure the intervention is high-quality, thorough, and clinically relevant. Offering all training content to the control arm after outcome evaluations demonstrates our commitment to ethical research principles and ensures equitable access to beneficial interventions for all participants [51]. Evaluating outcomes immediately after the training sessions and at one‑ and three‑month follow‑ups allows for assessment of the intervention’s durability. Long‑term outcome evaluation is vital in clinical research to determine the persistence and reliability of treatments and inform clinical decision‑making. This approach aids in understanding the longevity of behavioral and clinical changes and is essential for a comprehensive evaluation of intervention efficacy [52].

This study has several limitations, including the inability to fully blind participants to their assigned video intervention; however, data analysts will remain blinded to minimize bias. The generalizability of the findings from the selected hospitals affiliated with Shahid Beheshti University of Medical Sciences may be limited despite broad inclusion criteria. Additionally, while validated instruments will assess activation and adherence, they rely on self‑report and may be influenced by recall or social‑desirability bias. Another significant limitation is the potential for methodological contamination between study arms (e.g., participant-to-participant or staff-mediated sharing of intervention content), which may dilute actual intervention effects.

## Conclusion

This protocol explains a rigorous RCT intended to address crucial deficiencies in the present evidence concerning the utilization of interactive educational technologies among HD patients. This study compares interactive video, conventional video, and standard education to determine these interventions’ effectiveness and evaluate their comparative performance. The study benefits from enhanced internal validity and greater potential for external application through incorporating validated outcome measures, several follow-up evaluations, and a stringent implementation strategy. Interactive video education, if validated, presents a scalable, patient-focused strategy for enhancing activation, adherence, and clinical results in HD.
